#### Baseline

Following the enrolment appointment, participants will complete a 7-day food diary over the week leading up to the following appointment, the baseline (T0). Participants not keeping sufficiently detailed diaries and those eating meat on less than five eating occasions over the week will be discontinued. At the baseline appointment, an appropriately trained member of the research team will collect participants’ food diaries, ask participants to answer the baseline online questionnaire and measure participants blood lipids profile, blood pressure, weight and body composition. At the end of the baseline appointment, participants will be randomised to one of the two study conditions and will then follow the respective protocol for the next 4 weeks.

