### Sample size

Due to lack of research studies directly comparable to ours, pragmatic considerations have guided the decision to terminate recruitment once a sample of at least 100 volunteers has completed the 4 weeks follow-up. A power analysis based on this pragmatically selected sample size suggests that 100 participants completing the primary outcome will allow detection of a medium effect size of d=0.6 with a power of 1-beta=0.84 and a two-tailed alpha criterion of 0.05.

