### Randomisation and blinding

Participants’ group allocation will be based on a computer-generated randomisation sequence, produced by an independent statistician. The randomisation sequence was designed to individually allocate participants to the intervention or control condition in a 1:1 ratio and to achieve a proportional gender balance in the two conditions through blocking and stratification by sex. The research team is blinded to the randomisation sequence and to its block sizes and sequence. Allocation will be revealed to the researcher performing the randomisation only after the first food diary has been returned. Due to the nature of the intervention, participants and some members of the research team cannot be blind to participants’ group allocation. The members of the research team analysing the food diaries will be blind to the group allocation. Due to the nature of the outcomes, the risk of investigator bias will be low. To address the risk of social desirability bias in participants’ reporting of foods intake and questionnaire responses, participants will be reminded during the enrolment visit and before each questionnaire that there are no right or wrong answers.

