### Outcomes

#### Primary outcome

Change in mean daily grams of meat consumed between the baseline (T0) and the 4-week follow-up (T1).

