### Statistical analyses

We will employ linear models to investigate whether changes in meat consumption between the baseline and both follow-up differ significantly between the intervention and the control group. Our main analysis will employ unadjusted models and only include data from participants completing the relevant follow-up. Sensitivity analysis will be performed with a baseline observation carried forward assumption for missing data and adjusting for baseline variables. The intervention effect will be reported with 95% CI and p values. A two-tailed criterion p value of alpha=0.05 will be used to assess the statistical significance of the results. The same procedure will be employed to assess whether changes in the other prespecified dietary, nutritional, psychosocial and biophysical outcomes between the baseline and both follow-up differ significantly between the control and the intervention group. Detailed main, subgroup and sensitivity analyses plans will be finalised before conducting any specific outcome analysis. No interim analysis is planned.

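### The only named missing-data check, baseline observation carried forward, sets every missing change to zero: it tests one fixed scenario, understates uncertainty and is not reliably conservative

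*Protocol article*

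**What the plan says.** The Statistical analyses section fixes two choices. The main analysis uses unadjusted linear models that "only include data from participants completing the relevant follow-up". The check is then: "Sensitivity analysis will be performed with a baseline observation carried forward assumption for missing data and adjusting for baseline variables". The same procedure is carried over to the other dietary, nutritional, psychosocial and biophysical outcomes. No other missing-data method is named, and the detailed sensitivity plan is to be settled before any outcome is analysed.

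Three other sections bear on this:
- **Baseline:** the week recorded before T0 also serves as a screen, because "those eating meat on less than five eating occasions over the week will be discontinued".
- **Sample size:** the plan is to "terminate recruitment once a sample of at least 100 volunteers has completed the 4 weeks follow-up". This protects the number of completers but sets no limit on dropout.
- **Retention:** the principal investigator may discontinue participants who become ineligible or deviate significantly. Data from people who withdraw are kept for possible exploratory and sensitivity use.

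**The concern.** The primary outcome is a change from baseline, so BOCF enters a change of zero for every person without a follow-up diary. The model then treats these zeros as measurements. Three consequences follow.

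- **One scenario only.** The analysis shows what happens if dropouts did not change at all. It cannot show how large a departure would be needed to overturn the result.
- **Precision rises as data are lost.** The imputed values carry no uncertainty of their own.
- **The direction of bias is not fixed.** It depends on dropout in each arm and on whether controls change. Participants know their allocation and only one arm receives free food and materials, so dropout may differ by arm.

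Zero change is plausible for some people who leave the intervention, but doubtful as a general rule. The screening diary is also the baseline, so some regression to the mean is possible in both arms.

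At stake is how agreement or disagreement between the completer and BOCF results is read. If BOCF is presented as the conservative check, it may reassure or alarm for reasons unrelated to the reasons for dropout.

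**Working it through.** **1. The plan's own figure.** The Sample size section states that "100 participants completing the primary outcome will allow detection of a medium effect size of d=0.6 with a power of 1-beta=0.84", with "a two-tailed alpha criterion of 0.05". With 50 per arm, the noncentral t distribution (98 df) gives power 0.844 and the normal approximation gives 0.851. The 0.84 reproduces. It is stated for completers, so this point does not affect it.

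**2. Inputs.** From the article: 1:1 allocation, 100 completers, outcome as change from baseline. Assumed, because the article gives none: SD of intake 70 g/day with correlation 0.5 between diaries, so SD of change = 70 × √(2 × (1 − 0.5)) = 70; mean change -60 (intervention) and -20 (control), a true difference of -40; 50 randomised per arm; dropout unrelated to outcome within arm.

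**3. Expected BOCF estimate.** With dropout pI and pC and mean changes mI and mC, this is (1 − pI) × mI − (1 − pC) × mC. Coverage and type I error are from simulation.

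| Dropout, intervention / control | Calculation | BOCF estimate (g/day) | Result |
|---|---|---|---|
| 5% / 5% | 0.95×(-60) − 0.95×(-20) | -38 | coverage 0.95 |
| 10% / 10% | 0.90×(-60) − 0.90×(-20) | -36 | coverage 0.94 |
| 20% / 20% | 0.80×(-60) − 0.80×(-20) | -32 | coverage about 0.90 |
| 20% / 5% | 0.80×(-60) − 0.95×(-20) | -29 | coverage about 0.87 |
| 5% / 20% | 0.95×(-60) − 0.80×(-20) | -41 | slightly exaggerated |
| 5% / 20%, no effect (-20 in both arms) | 0.95×(-20) − 0.80×(-20) | -3 | type I error about 5.5% |

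Attenuation does not need a control change. With changes of -40 and 0 and 20% dropout in each arm, BOCF still gives -32, with coverage 0.89.

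**4. Standard error at 20% / 20%.** With no missing data it is √(2 × 4900 / 50) = 14.0. For completers (40 per arm) it is √(2 × 4900 / 40) = 15.7. Under BOCF the variance in each arm is (1 − p)σ² + p(1 − p)m²: intervention 3920 + 576 = 4496, control 3920 + 64 = 3984. The SE is √((4496 + 3984) / 50) = 13.0. Losing a fifth of the data gives a smaller SE than losing none.

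**5. Second calculation, in SD units.** Here the trial reaches about 50 completers per arm (63 randomised per arm at 20% dropout) and the true effect is -0.6 SD. BOCF gives -0.57, -0.54 and -0.48 at 5%, 10% and 20% equal dropout. At 20%, coverage is 88.5% against 95.2% for completers, and the SE is 0.162 against 0.199. With both arms changing by -0.4 SD, no effect, and 5% / 20% dropout, type I error is 6.8%.

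**6. When BOCF is right, and when it is too mild.** Suppose completers differ by -0.6 SD, controls do not change, and 20% of the intervention arm drop out. If those dropouts return to baseline, the true effect over all randomised is 0.8 × (-0.6) = -0.48, and BOCF is correct. If they end 0.6 SD above baseline, it is -0.48 + 0.2 × 0.6 = -0.36, while BOCF still gives -0.48. BOCF is therefore not a worst case.

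**7. Size of regression to the mean.** The screen counts eating occasions, not grams. Assume bivariate normality, SD 70, between-diary correlation 0.5, and a correlation ρ of occasions with grams. The induced change is then -70 × (1 − 0.5) × ρ × λ, where λ is the standardised lift in mean occasions among those kept. Removing 5% (λ = 0.109) with ρ = 0.5 gives about -2 g/day; removing 20% (λ = 0.350) with ρ = 0.7 gives about -9. The assumed control change of -20 is larger than the screen alone would produce in this range.

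**The case against.** The strongest reply is that BOCF is only a sensitivity analysis and the detailed plan is explicitly deferred. The absence of a tipping-point analysis or multiple imputation from a condensed article is therefore not an error. That stands, and this point does not rest on their absence. It rests on the method the article does name, which the deferral does not withdraw.

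Several stronger readings are tempting, and the document does not support them.

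- **That the primary estimate is biased.** The figures above assume dropout unrelated to outcome within arm, where the completer analysis is unbiased. They describe the sensitivity estimate only.
- **That zero is systematically the wrong value.** The article gives no dropout rate, reasons for dropout or control change. Return to habitual eating is plausible for someone who leaves a programme supplying free food.
- **That BOCF creates a spurious benefit.** In the no-effect case the bias is about -3 g/day against an SE of about 13.
- **That BOCF says nothing about robustness.** It examines one departure, and surviving it is limited information.

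It is also fair that distortion is modest at low dropout, and that reminders and payment for assessment visits may keep dropout low.

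**Conclusion.** The concern holds as a weakness of the named sensitivity analysis. BOCF tests one fixed departure from the completers' assumption, counts imputed zeros as data, and can err in either direction. Under the assumed SD and mean changes, the error on a true -40 g/day difference is about 2 g/day at 5% dropout per arm, 4 at 10% and 8 at 20%, and 11 when 20% of the intervention arm and 5% of controls drop out. Coverage falls to about 0.90 and 0.87 in the last two cases. The error is thus minor at low, balanced dropout and material at about 20% or with clear imbalance. Every g/day figure rests on inputs that the article does not supply, including the size of any regression to the mean. The stated power is unaffected. The change is worth making before the plan is closed, but nothing here shows that the trial's main result would be wrong.

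**What to change.** Before the analysis plan is finalised:

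1. Include all randomised participants with observed data in one mixed model for meat intake at T0, T1 and T2, with arm by time, a common baseline mean and sex. Read the T1 contrast as primary and the T2 contrast as secondary. Alternatively, use multiple imputation with baseline, the other follow-up, arm and sex.
2. Make delta-adjusted (tipping-point) multiple imputation the missing-data sensitivity analysis. Shift the imputed values by increasing amounts, separately by arm, and report the shift at which the conclusion changes.
3. Keep BOCF, if wanted, only as a supplement, and do not describe it as conservative.

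The cost is plan wording and a little programming; trial conduct does not change. The main model would rely on data being missing at random, which the delta analysis then examines. The gain at T1 is limited for people who miss both follow-ups, because only baseline and sex then inform their missing values.

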### Qualitative study

After the 8-week follow-up, a subsample of participants receiving the intervention will be invited to take part in a semistructured interview. This qualitative study aims to understand participants’ experiences of the intervention, the mechanisms through which the intervention helped reducing meat consumption or the barriers preventing the intervention to aid this transition. The semistructured interviews will follow a discussion guide while also remaining sensitive to unsolicited themes. The interview will set the context by asking participants to elaborate on their motivation to volunteer for the trial and on their thoughts and feelings towards reducing meat consumption prior to enrolling into the study. Participants will then be encouraged to elaborate on the mechanisms through which they felt that the intervention helped them eat less meat or the barriers preventing the intervention to do so. In doing so, participants will be prompted to think about the intervention in its entirety as well as about each individual intervention component. Participants will be encouraged to elaborate on their perceived ability and motivation to maintain a lower consumption of meat after the intervention period and beyond the context of the study. Whenever possible we will use open questions to encourage participants to elaborate on their thoughts and feelings freely and in depth. We aim to avoid questions of evaluative nature to minimise the risk of social desirability bias. We anticipate interviewing 20 participants, however, sampling will be extended should new themes emerge during the interviewing process. We will employ a purposeful sampling technique aiming to achieve a sex balance. Participants will be free to decide whether or not to be interviewed. No additional compensation will be offered to participants agreeing to be interviewed. Qualitative interviews will be conducted in person and transcribed verbatim. Transcriptions will be analysed using NVivo and employing a data-driven thematic analysis to identify codes and to group these codes into broader themes.

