### Objectives

The primary aim of the replacing meat with alternative plant-based products (RE-MAP) trial is to examine the effectiveness of a behavioural intervention to reduce meat consumption compared with a no intervention control condition. Additionally, this study will evaluate the impact of the intervention on the consumption of other food groups, the nutritional composition of participants’ diets, the putative psychosocial determinants of eating a low meat diet and of using plant-based meat alternatives and on biological markers of health risk, including blood lipid profiles, blood pressure, weight and body composition. This study also aims to qualitatively investigate participants’ experiences of the intervention, the mechanisms through which the intervention reduced meat consumption, and/or the barriers preventing the intervention to aid this dietary transition.

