### Measurements

Table 2 provides a summary of the trial activities and of the measurement that will be collected at each stage of the trial.

**Table 2 T2:** Schedule of measurements and trial activities

	Visits				
	Telephone screening	Enrolment visit	Baseline visit	4-week follow-up	8-week follow-up
Enrolment					
Eligibility screening	X				
Informed consent		X			
Randomisation			X		
Intervention					
Replacing meat with alternative plant-based product					
Control					
Demographic and psychosocial traits					
Demographics			X		
Food neophobia			X		
Self-control scale			X		
Dietary measurements					
Food diary			X	X	X
Retrospective eating questionnaire			X	X	X
Psychosocial variables					
Attitude towards eating a low meat diet and using meat alternatives			X	X	X
Perceived behavioural control of eating a low meat diet and using meat alternatives			X	X	X
Subjective social norm of eating a low meat diet and using meat alternatives			X	X	X
Intention to eat a low meat diet and to use meat alternatives			X	X	X
Attachment to meat			X	X	X
Eating identity			X	X	X
Desire for similarity between meat and meat alternatives			X	X	X
Biophysical outcomes					
Height			X		
Weight			X	X	X
Body composition			X	X	X
Blood pressure			X	X	X
Blood lipids profile			X	X	X
Qualitative workstream					
Semistructured interviews					X

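### Interview sampling names only sex balance and starts after the 8-week visit, so participants who reduced little may be few and early leavers are probably missed, although barriers are a stated objective

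*Protocol article*

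**What the plan says.** The Objectives section of the protocol article includes a qualitative aim covering participants' experiences and "the mechanisms through which the intervention reduced meat consumption, and/or the barriers preventing the intervention to aid this dietary transition". The Qualitative study section repeats it: "the mechanisms through which the intervention helped reducing meat consumption or the barriers preventing the intervention to aid this transition".

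The same section fixes who is approached and when:

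- Timing and source: "After the 8-week follow-up, a subsample of participants receiving the intervention will be invited to take part in a semistructured interview". The schedule in Table 2 has one mark for interviews, which reads as the 8-week column (the table layout is partly broken).
- Criterion: "We will employ a purposeful sampling technique aiming to achieve a sex balance". No other characteristic is named.
- Number: "We anticipate interviewing 20 participants, however, sampling will be extended should new themes emerge during the interviewing process".
- Conditions: taking part is voluntary, in person and carries no extra payment.

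The Retention section allows withdrawal at any time and keeps the data of those who withdraw. It mentions no exit contact or interview.

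**The concern.** Purposive sampling selects people for what they can tell about the question. Here the question is what helped and what stood in the way, so the informative characteristics are how far a participant reduced meat intake and whether they stayed in the study. Neither is a criterion. Sex is, but the article does not tie sex to the qualitative question.

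The timing adds to this. Someone who left the study early, possibly because of a barrier, has no stated route to an interview. At stake is the barriers part of the qualitative objective: it could rest largely on people for whom the intervention worked, and new themes could stop appearing before the other accounts have been heard.

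**Working it through.** **The plan's own figure.** The plan gives no figure for the composition of the interview sample. Its one formal calculation, power 0.84 for d = 0.6 with 100 completers, reproduces: 0.844 by the noncentral t with 98 degrees of freedom. The point does not depend on it.

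**Inputs from the protocol**
- At least 100 participants completing the 4-week follow-up (T1) (Sample size) and 1:1 allocation (Randomisation and blinding), so about 100/2 = 50 in the intervention arm. Taking all 50 as available after T2 is an assumption.
- 20 interviews (Qualitative study).

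**Assumed inputs**
- The number K of the 50 who did not reduce meat: 5, 10 or 14. The protocol gives no share. The value 14 comes from the planning effect. If d = 0.6 is on the standard deviation of change, change is normal and the control mean change is zero, the share with no reduction is Φ(−0.6) = 0.274, and 0.274 × 50 = 13.7.
- Willingness: equal, or non-reducers with half the odds of being recruited at each draw.

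**Equal willingness.** Selection ignores response, so the number X of non-reducers interviewed is hypergeometric:

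P(X = x) = C(K, x) · C(50 − K, 20 − x) / C(50, 20)

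For K = 5: P(0) + P(1) + P(2) = 0.067 + 0.259 + 0.364 = 0.690.
For K = 10: 0.003 + 0.028 + 0.108 = 0.139.
For K = 14: 0.0002 + 0.0026 + 0.0175 = 0.020.

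**Half the odds.** The same draw with weight 0.5 on non-reducers (Wallenius noncentral hypergeometric).

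| Non-reducers among 50 | Expected among 20, equal willingness | P(at most 2), equal willingness | P(at most 2), half the odds |
|---|---|---|---|
| 5 | 2.0 | 69% | 92% |
| 10 | 4.0 | 14% | 52% |
| 14 | 5.6 | 2% | 22% |

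**Early leavers.** No probability is needed. Invitation follows T2, the schedule shows no earlier interview, and no contact with those who withdraw is described. Under the plan as written, they are probably not interviewed.

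**The extension rule.** Sampling goes beyond 20 if new themes emerge. The trigger is what the people already interviewed say. Nothing sends the additional invitations to non-reducers or early leavers.

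**The case against.** The strongest reply is that the plan is adequate for a small qualitative component and that the article condenses a fuller protocol. Much of this stands:

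- Every interviewee is asked about barriers, overall and for each component, with open and non-evaluative questions. Partial reducers, and those who went back to meat once the free food ended, can describe barriers too.
- Interviewing after T2 suits the question about maintaining the change.
- Non-reducers who complete the study remain eligible, and a random draw would mirror the arm. With 14 of 50 non-reducers and equal willingness, three or more would be interviewed with 98% probability.
- Neither the halved odds nor the idea that unpaid interviews attract satisfied participants has a source in the protocol.

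The condensation argument carries less weight. The article does not merely leave the sampling frame out; it states a criterion and a time point, and the point concerns those.

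A reader might infer that drop-outs are excluded, or that the interviews will be one-sided. The protocol supports neither. It speaks of participants receiving the intervention, not of completers, and someone who stopped using the products but still attends can be invited. It also does not say that sex is the sole criterion; it simply names no other.

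**Conclusion.** The point holds as a mismatch between a stated aim and a stated sampling rule, and it is minor. Selection by sex, after T2, does nothing to ensure that participants who reduced little are heard, and it probably misses those who stop early.

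How much this matters depends on assumptions that the protocol cannot settle. With equal willingness the chance of at most two non-reducers runs from 69% down to 2% as their number rises from 5 to 14 of 50; with half the odds it runs from 92% down to 22%. The risk is therefore material when non-reducers are uncommon or less willing, and small when they are common and equally willing.

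It would be too strong to conclude that the barriers question cannot be answered, because the interview guide and the extension rule both help. The primary outcome, the sample size and the error rates are not touched.

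**What to change.** In the Qualitative study section:

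1. Sample purposively for variation in self-reported change in meat-eating occasions (baseline to T1 or T2) as well as for sex. Set no fixed quota. Requiring one third of 20, about 7, could not be met if only 5 participants failed to reduce.
2. Also invite intervention participants who stop before T2 and still agree to be contacted.

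In the Dietary measurements section, allow the retrospective eating questionnaire to be used for interview sampling; at present it is reserved for sensitivity analyses. It is already collected at baseline, T1 and T2. It counts occasions, not grams, which is enough to sort people for interview. The diaries are less suitable, because grams of meat must first be disaggregated by staff blinded to allocation.

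Someone other than the blinded diary analysts should make the selection.

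The cost is a small administrative step, and the person inviting will know the self-reported change. The planned number of interviews stays at about 20, and no new measurement is needed.
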